## **5. DISCONTINUATION OF STUDY INTERVENTION AND PARTICIPANT WITHDRAWAL**

Discontinuation of treatment intervention dose not represent withdrawal from the study. As certain data on clinical events beyond study intervention discontinuation maybe important to the study, they must be collected through the participant's last scheduled follow-up, even if the participant has discontinued study intervention. Therefore, all participants who discontinue study intervention prior to completion of the protocol-specified treatment period will still continue to participate in the study for survival follow-up.

### **5.1 Patient Discontinuation**

Patient have the right to voluntarily withdraw from the study at any time for any reason. In addition, the investigator has the right to withdraw a patient from the study at any time. Reasons for withdrawal from the study may include but are not limited to the following:

- 379 • Patient withdrawal of consent at any time
- 380 • Any medical condition that the investigator or sponsor determines may jeopardize the
- 381 patient's safety if he or she continues in the study
- 382 • Investigator or sponsor determines it is in the best interest of the patient
- 383 • Patient non-compliance

384 Every effort should be made to obtain information on patients who withdraw from the study.  
385 The primary reason for withdrawal from the study should be documented. However, patients  
386 will not be followed for any reason after consent has been withdrawn.

## 387 **5.2 Study Treatment Discontinuation**

388 Permanent discontinuation of study treatment if one of the following occurs:

- 389 • Patient decision
- 390 • Loss to follow-up
- 391 • Severe non-compliance to the study protocol
- 392 • One or more of the exclusion criteria being met at study entry
- 393 • Adverse event contraindicating further treatment
- 394 • Initiation of alternative bridging therapy including locoregional therapy and/or
- 395 anticancer therapy
- 396 • Confirmed disease progression
- 397 • Pregnancy or intent to become pregnant

## 398 **5.3 Study Discontinuation**

399 The investigators have the right to terminate this study at any time. Reasons for terminating  
400 the study may include but are not limited to the following:

- 401 • The incidence or severity of adverse events in this or other studies indicates a
- 402 potential health hazard to patients
- 403 • Patient enrollment is unsatisfactory
- 404 • Excessively slow recruitment
- 405 • Poor protocol adherence
- 406 • Inaccurate or incomplete data recording
- 407 • Non-compliance with the International Conference on Harmonization (ICF) guideline
- 408 for Good Clinical Practice

## 409 **5.4 Withdrawal of Consent**

410 Patients are free to withdraw from the study at any time without prejudice to further  
411 treatment.

412 Patients who withdraw consent for further participation in the study will not receive SBRT (if  
413 not done), but will continue to be observed during future follow-up visits for progressive

disease and survival, which will continue until the end of the study unless the patient has expressly withdrawn their consent to survival follow-up. Note that the patient may be offered additional tests or tapering of treatment to withdraw safely.

A patient who withdraws consent will always be asked about the reason(s) for withdrawal and the presence of any adverse events (AEs). The Investigator will follow up AEs outside of the clinical study.

If a patient withdraws consent, they will be specifically asked if they are withdrawing consent to:

- all further participation in the study including any further follow up (e.g., survival contact telephone calls)
- withdrawal of consent to the use of their study generated data
- withdrawal to the use of any samples (if any)

## **6. STUDY ASSESSMENTS AND PROCEDURES**

The following procedures will be performed during the screening visit:

- Informed Consent
- Review of eligibility criteria
- Medical history and demographics
- Complete physical exam
- ECOG Performance Status
- Vitals signs, weight and height
- Blood for Hepatitis B viral (HBV) serology including surface antigens of Hepatitis B virus (HBsAg), antibody against the surface antigen (Anti-HBs) and HBV DNA, and Hepatitis C viral (HCV) serology with anti-HCV.
- Review of prior/concomitant medications
- Imaging by MRI with gadoxetate disodium, dual-tracer (FDG and ACC) PET-CT with contrast-enhanced CT scan. The scanning algorithms of MRI with gadoxetate disodium and dual-tracer PET-CT scan are shown in APPENDIX 2 and APPENDIX 3.
- Clinical laboratory tests for:
  - Hematology
  - Clinical biochemistry
  - Coagulation profile (PT, PTT, INR)
  - Creatinine clearance

- 449           ○ Serum pregnancy test (for women of childbearing potential only)  
450           ○ Hepatitis serologies including Hepatitis B virus (HBV) and Hepatitis C virus  
451           (HCV) as mentioned above.

## 452   **6.1   Informed Consent**

453   The investigator or designee must obtain documented consent from each potential participant  
454   or each participant's legally acceptable representative prior to participating in a clinical study.  
455   Consent must be documented by the participant's dated signature or participant's legally  
456   acceptable representative's dated signature on a consent form along with the dated signature  
457   of the person conducting the consent discussion.

458   A copy of the signed and dated consent form should be given to the participant before  
459   participation in the study.

## 460   **6.2   Inclusion/Exclusion Criteria**

461   All inclusion and exclusion criteria will be reviewed by the investigator to ensure that the  
462   participant is eligible for the study before starting study intervention.

## 463   **6.3   Medical History**

464   Medical history will be obtained by the investigator or designee. The medical history will  
465   collect all active conditions and any condition diagnosed within the prior 10 years that the  
466   investigator considers to be clinically significant.

## 467   **6.4   Concomitant Medications**

468   Therapies considered necessary for the patient's well-being may be administered at the  
469   discretion of the Principle Investigator and/or co-investigators. All medications administered  
470   at the start of study drug through last dose of study drug must be recorded on the appropriate  
471   source documents.

### 472   **6.4.1   Permitted concomitant medications**

| Supportive medication/class of drug:                                                                                                                                                                                   | Usage:                                        |
|-------------------------------------------------------------------------------------------------------------------------------------------------------------------------------------------------------------------------------|------------------------------------------------------|
| Concomitant medications or treatments (e.g., acetaminophen or diphenhydramine) deemed necessary to provide adequate prophylactic or supportive care, except for those medications identified as "prohibited," as listed above | To be administered as prescribed by the Investigator |

|                                                                                                                                                                                                                   |                                                  |
|-------------------------------------------------------------------------------------------------------------------------------------------------------------------------------------------------------------------|--------------------------------------------------|
| Best supportive care (including antibiotics, nutritional support, correction of metabolic disorders, optimal symptom control, and pain management [including palliative radiotherapy to non-target lesions, etc]) | Should be used, when necessary, for all patients |
| Inactivated viruses, such as those in the influenza vaccine                                                                                                                                                       | Permitted                                        |

## 473 6.4.2 Excluded concomitant medications

| Prohibited medication/class of drug:                                                                                                                                                             | Usage:                                                                                                                                                                                                                                                                                                                                                             |
|--------------------------------------------------------------------------------------------------------------------------------------------------------------------------------------------------|--------------------------------------------------------------------------------------------------------------------------------------------------------------------------------------------------------------------------------------------------------------------------------------------------------------------------------------------------------------------|
| Any investigational anticancer therapy other than those under investigation in this study                                                                                                        | Should not be given concomitantly whilst the patient is on study treatment                                                                                                                                                                                                                                                                                         |
| mAbs against CTLA-4, PD-1, or PD-L1 other than those under investigation in this study                                                                                                           | Should not be given concomitantly whilst the patient is on study treatment                                                                                                                                                                                                                                                                                         |
| Any concurrent chemotherapy, targeted therapy, immunotherapy, biologic or hormonal therapy, or any forms of radiotherapy for cancer treatment other than those under investigation in this study | Should not be given concomitantly whilst the patient is on study treatment. (Concurrent use of hormones for non-cancer-related conditions [e.g., insulin for diabetes and hormone replacement therapy] is acceptable. Local treatment of isolated lesions, excluding target lesions, for palliative intent is acceptable [e.g., by local surgery or radiotherapy]) |
| Herbal and natural remedies which may have immune-modulating effects                                                                                                                             | Should not be given concomitantly unless agreed by the sponsor                                                                                                                                                                                                                                                                                                     |

## 474 6.5 Efficacy Assessments

475 Screening assessments must include magnetic resonance imaging (MRI) with gadoxetate  
476 disodium as well as dual-tracer PET-CT with contrast enhanced triphasic CT scan of the liver  
477 for tumor contouring and treatment planning for SBRT.

478 Follow-up imaging with MRI with gadoxetate disodium injection and dual-tracer PET-CT  
479 scan with contrast-enhanced triphasic CT scans every 3 months after SBRT will be arranged  
480 for treatment response evaluation by RECIST 1.1, mRECIST, and PERCIST  
481 (APPENDIX 4 and APPENDIX 5) and surveillance for recurrence/relapse.

482 At the investigator's discretion, scans should be repeated at any time if progressive disease is  
483 suspected.

484 Confirmation of progression guidelines are set for the following reasons:

- 485 • for patient management and treatment decisions
- 486 • when scans are evaluated by two independent radiologists.

Confirmed objective disease progression refers to either of the following scenarios: 1. clinical progression/deterioration followed by a radiologic verification scan (progressive disease [PD] by RECIST 1.1, mRECIST, and PERCIST); or 2. in the absence of significant clinical deterioration, radiologic PD by RECIST 1.1, mRECIST, and PERCIST followed by a second radiologic confirmation scan with PD assessed according to the specific confirmation of progression criteria listed below. The confirmatory scan should occur preferably at the next scheduled imaging visit and no earlier than 4 weeks following the date of the immediate prior assessment of PD.

Immediate prior radiologic progression would be considered confirmed if any the following criteria are met in the confirmatory scan:

- $\geq 20\%$  increase in the sum diameters of target lesions (TLs) compared with the nadir at 2 consecutive visits, with an absolute increase of at least 5 mm in sum of diameters compared to nadir,

- and/or significant progression (worsening) of non-target lesions (NTLs) and/or of pre-existing new lesions at the confirmatory scan time-point compared with the immediate prior time-point (Note: Pre-existing new lesions are evaluated as NTLs at the confirmatory scan time-point),

- and/or additional new unequivocal lesions at the confirmatory scan time-point.

If progression is not confirmed, in the absence of significant clinical deterioration, then the patient should continue the study and on-treatment assessments until the next PD which will also require a follow-up confirmation scan. If the first PD is not confirmed by the immediate next scan, then the Investigator should not change the PD assessment of the first scan.

If a patient discontinues treatment (and/or receives a subsequent anticancer therapy) prior to radiologic progression, then the patient should still continue to be followed until confirmed objective disease progression.

Following confirmed progression, patients should continue to be followed up for survival every 2-3 months until death or until patient refusal.

Please refer to APPENDIX 4 and APPENDIX 5 for the definitions of objective response by RECIST 1.1, mRECIST, and PERCIST. The method of determination of metabolic tumor volume (MTV) and total lesion glycolysis (TLG) and total lesion activity (TLA) based on PET-CT scan with FDG and ACC respectively for subsequent exploratory statistical analyses were described in APPENDIX 5.

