## **8.1 Analysis Endpoints**

### **8.1.1 Efficacy Endpoint**

#### **Primary**

- Progression-free survival (PFS)
  - PFS is calculated from the start of SBRT to the date of radiologically confirmed progressive disease based on RECIST 1.1, mRECIST, and PERCIST, or death from any cause
- Best objective response as defined by RECIST 1.1, mRECIST, and PERCIST

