**APPENDIX 2. Scanning algorithm of magnetic resonance imaging (MRI) scan with gadoxetate disodium injection**

MRI scanning was conducted with a 3-Tesla MR scanner (Philips Achieva 3.0T TX, Philips Medical Systems, Best, The Netherlands) throughout the whole study as shown below. The same scanner is used for all scans for all patients recruited into this study. MRI scans were performed at baseline, then at every 3 months until liver transplantation was performed or progressive disease was observed, whichever came earlier. All HCC lesions were evaluated by two independent radiologists and any discrepancy in determining the nature of the lesions was solved by consensus.

(1) T2-weighted TSE single-shot in 5mm section thickness

(2) Breath-hold triggered T1-weighted in-phase and opposed sequences in 7mm section thickness

(3) T2-weighted SPAIR with TE 80 and 160 in 7mm section thickness

(4) Diffusion-weighted single-shot echo planar imaging with respiratory triggering

(5) Gadoxetate disodium (0.025mmol/kg body weight)-enhanced dynamic phases: unenhanced, late arterial-phase, portal-venous phase, and delayed phases with T1-weighted three-dimensional (3D) turbo-field-echo sequence (T1 high-resolution isotropic volume examination, THRIVE) with a 2-mm section thickness and a FOV of 32-38 cm.

1038

1039 **APPENDIX 3. Positron-emission tomography with integrated contrast-enhanced computed**  
1040 **tomography (PET-CT) with two radiotracers (C-acetate [ACC] and F-**  
1041 **fluorodeoxyglucose [FDG])**

1042 Dual Tracer PET-CT scan was performed at baseline, and then every 3 months after SBRT  
1043 until liver transplantation done or until progressive disease whichever came earlier. All scans  
1044 were performed using the same scanner and protocol (Discovery VCT, 64-MDCT; GE  
1045 Healthcare Bio-Sciences Corp., Piscataway, New Jersey, USA). All patients are required to fast  
1046 for  $\geq 6$  hours, and the blood glucose concentration is  $\leq 8$  mmol/L before radiopharmaceutical  
1047 injection. ACC (440–590 MBq; 8.0 MBq/kg of body weight) was then administered  
1048 intravenously, and limited upper abdomen coverage acquired at 1 minute followed by a whole  
1049 body imaging is performed at 11 minutes after injection. Data acquisition with an integrated in-  
1050 line PET-CT scanner (Discovery VCT, 64-multislice CT; GE Healthcare Bio-Sciences Corp, NJ)  

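### Read with Section 6.5, the co-primary PFS definition leaves out a first progression that is followed by transplantation or new anticancer therapy before the confirmatory scan

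*Protocol*

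**What the plan says.** Section 8.1.1 of the protocol lists PFS first among its primary endpoints: "PFS is calculated from the start of SBRT to the date of radiologically confirmed progressive disease based on RECIST 1.1", mRECIST and PERCIST, or death from any cause.

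Section 6.5 defines confirmed progression by two routes.

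- Route 1 is "clinical progression/deterioration followed by a radiologic verification scan". One scan after the deterioration is enough.
- Route 2, open only to patients without significant clinical deterioration, is PD on imaging "followed by a second radiologic confirmation scan with PD assessed according to the specific confirmation of progression criteria listed below". The second scan may not come within 4 weeks of the first and should preferably be the next planned imaging visit, which is 3-monthly.

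The same section gives patient management and evaluation by two radiologists as the reasons for confirmation. It adds that a first PD reading stays as it is if the next scan does not confirm it. The patient then continues to the next PD, which again needs confirmation.

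On treatment changes, Section 6.5 deals with a patient who stops treatment or starts other anticancer therapy "prior to radiologic progression, then the patient should still continue to be followed until confirmed objective disease progression". Section 5.2 lists "Initiation of alternative bridging therapy including locoregional therapy and/or" anticancer therapy as a reason to stop study treatment.

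Appendix 2 schedules MRI "every 3 months until liver transplantation was performed or progressive disease", whichever is earlier. Appendix 3 says the same for PET-CT, and the synopsis (Study Design) also ends imaging at transplantation or PD.

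**The concern.** In a bridging trial, the weeks after a first PD are when a patient may receive a liver or be given another treatment. The two size criteria do not exclude each other. A solitary 2 cm tumour that grows to 3 cm has increased by 50% and by 10 mm. That exceeds the 20% and 5 mm thresholds, yet the tumour is well below the 6.5 cm UCSF limit in Section 3.1.

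If PD counts only once it is confirmed, the first PDs that go uncounted are not a random subset. They are the ones overtaken by transplantation or that prompted treatment. Leaving them out moves PFS in one direction only, upward. PFS is a co-primary endpoint and the trial has a single arm, so no comparison group carries the same bias.

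**Working it through.** **The plan's own figure.** The protocol gives no PFS rate, target or transplant rate. Its only design calculation concerns objective response (Section 8: p0 = 0.60, p1 = 0.85, two-sided alpha 0.05, power 80%, N = 28).

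- Normal approximation: n = [(1.960·√(0.60·0.40) + 0.842·√(0.85·0.15)) / 0.25]² = 25.4, so 26.
- With continuity correction: (25.4/4)·[1 + √(1 + 2/(25.4·0.25))]² = 29.3, so 30.
- The stated 28 lies between these, and 28/(1 − 0.20) = 35 also reproduces. PFS does not enter, so N is not touched.

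**The texts side by side.** Section 8.1.1 runs PFS "to the date of radiologically confirmed progressive disease" and does not itself define confirmation. Section 6.5 does. Take a patient with a first PD and no deterioration, who can be confirmed only by route 2:

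| What happens before the second scan | Result as written |
|---|---|
| Transplantation | Imaging has ended, so no second scan. Not an event, unless a later death is counted |
| Other anticancer therapy | A scan may still be done, but it can reflect the new therapy and fail to confirm. Section 6.5 covers only therapy started before radiologic PD |
| Deterioration, further scan showing PD | Route 1 is met. Event |
| Deterioration, no further scan | Route 2 is closed by the deterioration, and route 1 lacks its scan. Event only if the patient dies |

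The protocol also does not say whether a confirmed PD is dated to the first or the second scan.

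**Illustrative size (all inputs assumed).** Times to PD and to exit (transplantation or other therapy) are exponential. Median time to PD is 12, 18 or 24 months, and median time to exit 12 or 24 months. Scans are 3-monthly, and confirmation comes 1 or 3 months after the first PD. A confirmed PD is dated to the first scan; an unconfirmed one is censored at exit.

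The share q of first PDs overtaken by exit is 1 − exp(−gap·ln 2/median exit):

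- gap 1 month: 0.056 (exit median 12 months) or 0.029 (24 months)
- gap 3 months: 0.159 or 0.083

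If that share is removed from the PD hazard, 12-month PFS changes from S to about S^(1−q). With S = 0.50 and q = 0.159, 0.50^0.841 = 0.558. With S = 0.707 and q = 0.029, 0.707^0.971 = 0.714.

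Simulation with 40,000 patients per scenario, comparing the two rules on the same patients:

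| Median PD / exit (months) | Gap (months) | First PDs unconfirmed | 12-month PFS, first PD counts | 12-month PFS, confirmed only | Difference (points) |
|---|---|---|---|---|---|
| 12 / 12 | 1 | 5.7% | 49.5% | 51.7% | 2.2 |
| 12 / 12 | 3 | 16.2% | 50.2% | 56.4% | 6.2 |
| 12 / 24 | 1 | 2.8% | 49.7% | 50.8% | 1.1 |
| 12 / 24 | 3 | 8.3% | 49.8% | 53.0% | 3.2 |
| 18 / 12 | 3 | 16.0% | 62.4% | 67.6% | 5.2 |
| 24 / 12 | 3 | 15.8% | 71.0% | 75.2% | 4.2 |
| 24 / 24 | 1 | 2.7% | 70.6% | 71.3% | 0.7 |

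The scenarios not shown fall inside this range. Overall, 2.7% to 16.2% of first PDs go unconfirmed, and 12-month PFS rises by 0.7 to 6.2 points. For every 10 first PDs, that is 0.3 to 1.6 events.

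**The case against.** The best defence is that the protocol nowhere says an unconfirmed PD is censored. Radiologically confirmed in Section 8.1.1 could simply mean seen on imaging, since that section does not cite Section 6.5. The reasons given for confirmation concern patient management and reading, not PFS, and the first PD reading stays on record. Detailed censoring rules usually belong in a SAP, which is not shown here.

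This stands in part. It rules out saying that the protocol prescribes censoring. It does not remove the problem, because what counts as a PFS event is fixed in the protocol, and Section 6.5 is its only definition of confirmed progression. Keeping the first reading on record does not make it a PFS event.

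A reader might also infer that every progression needs a second scan, or that a patient who deteriorates is simply kept as progression-free. The text does not support either. Route 1 needs one scan, scans may be repeated whenever PD is suspected, and death is an event. Nor does other bridging therapy end follow-up: Section 5 continues data collection after study treatment stops, so some of these patients will still be scanned.

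On size, Section 6.5 permits a gap of 4 weeks, and Appendix 5 asks for most PERCIST progressions to be confirmed within 1 month, so the bias can be small. No PFS null value or target exists for it to overturn.

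**Conclusion.** The point holds in a limited form. Sections 8.1.1 and 6.5, read together, leave a first PD outside the PFS event when transplantation comes before the second scan, or when other therapy does so and the scan then fails to confirm. A narrower gap remains for PD followed by deterioration without a further scan or death. If these PDs are not counted, PFS is biased upward. The direction follows from the definition; the size does not.

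The range of about 1 to 6 points at 12 months rests on assumed medians and gaps, and on an exit rate that a first PD does not change. If PD prompts therapy, more events would be lost; if it delays transplantation, fewer.

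A reader might infer a much larger bias, for example a true 12-month PFS of 70% reported as 78% with a 6-month median wait for a liver, or as 81% to 86% if 30% to 50% of first PDs were treated otherwise first. The documents do not support those inputs. The synopsis gives 6 months as the lower end of the typical range (6 months to 4 years), and no source is given for the share treated otherwise. The sample size and the response endpoint are unaffected.

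**What to change.** Add to Sections 6.5 and 8.1.1, and carry into the SAP:

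> For PFS, a first PD with no evaluable confirmatory scan before liver transplantation, new anticancer therapy, clinical deterioration, death or loss to follow-up is an event on the date of the first PD scan. A confirmed PD is also dated to the first PD scan. A first PD is set aside only by an evaluable confirmatory scan taken before any of these events.

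Reconcile this with the synopsis (Study Design) and Appendices 2 and 3, which stop imaging at transplantation or PD, while Section 6.5 calls for a scan after the first PD. Continuing imaging to confirmation would not replace the rule, because a patient transplanted or treated in the interval would still lack an untainted second scan.

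The change needs no new data and no change in patient care. PFS becomes slightly less favourable, and a few false first PDs that can no longer be checked will count as events.
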